### Participants

We will report numbers of participants consented, randomised, and followed up in a Consolidated Standards of Reporting Trials (CONSORT) flowchart (Fig. 1). At the time of writing this SAP, recruitment of patients is on-going, and the trial teams remain unmasked; therefore, the aggregated values for the CONSORT flowchart are not provided here.

**Fig. 1 Fig1:**
[figure not shown]
Consolidated Standards of Reporting Trials (CONSORT) flowchart for the Positioning In Macular hole Surgery (PIMS) trial, with expected numbers at each stage

Baseline characteristics (variables measured preoperatively) will be summarised by positioning policy group. For continuous variables, we will examine the distribution of the data for symmetry, and report either the mean and SD, or the median and interquartile range (IQR) values. For categorical variables we will report the number and percentage in each category for categorical variables, with a note of numbers with missing data if any (see Additional file 1: Table S1).

### Analysis of primary outcome

This will be analysed using mixed-effects logistic regression. This analysis will be performed by the command *xtlogit* in Stata 14:

xtset site

xtlogit machole randgrp machsize i.lenstat, re

If the mixed regression model fails to converge, we will model site as a fixed effect rather than a random effect with the following command:

xtlogit machole randgrp machsize i.lenstat, fe

We will ensure that the quadrature approximation in our model is adequate and stable. First, we will run the command *quadchk* to test if our model is sensitive to changes in the number of adaptive points [7]. If the relative differences in our coefficients change by more than 1%, we will improve the quadrature approximation by increasing the number of integration points until this difference in coefficients is less than 1%. If this approach is not successful in achieving stable quadrature approximation, we will consider the command *gllamm* [8] which allows for adaptive quadrature numerical integration with the following command:

gllamm machole randgrp machsize i.lenstat, i(site) family(binom) link(logit) adapt

### Analyses of secondary outcomes

For the analysis of further surgery for macular holes, performed or planned, we will use logistic regression (*xtlogit*). Best-corrected visual acuity (BCVA), measured using Snellen charts at a standard distance of 6 m, will be transformed to a LogMAR scale with two decimal places [9], and then analysed using linear regression (*xtreg*). Measurements of BCVA corresponding to count fingers (CF), hand movements (HM), perception of light (PL), and no perception of light (NPL) will be replaced with values of 2.10, 2.40, 2.70, and 3.00, respectively. The number of patients in each BCVA category and their corresponding numerical values will be tabulated by treatment arm. For the patient-reported experience of positioning at 3 months, which is on the scale 0 (very difficult) to 10 (very easy) we will remain masked to treatment arm and consider an applicable cut-off value to dichotomise this variable and then use logistic regression (*xtlogit*). For the patient-reported outcome ‘Given what you know now, would you still have elected to have the operation?’ we will pool the responses ‘Don’t know’ and ‘No’ into one category, and use logistic regression (*xtlogit*). If the proportion of ‘Don’t know’ responses exceeds 10% (19 patients) we will undertake a sensitivity analysis by pooling the ‘Don’t know’ with ‘Yes’ responses and compare how this alternative pooling affects the odds ratio estimate. The Complications of Age-related Macular Degeneration Prevention Trial Research Group [10] observed a skewed distribution of the VFQ-25 score; therefore, we will assume that our results will be similarly skewed, and perform a logistic transformation (log(x/(100 − x))) of the VFQ-25 scores, and with this transformed outcome use linear regression (*xtreg*). When adjusting analyses of BCVA and VFQ-25 for their respective baselines we will use the same normalising transformation for the baseline measurement as for the follow-up measurement.

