## Overview

### Purpose and scope of statistical analysis plan (SAP)

The aim of this paper is to report, in detail, the planned analyses that were approved by the Trial Steering Committee for the principal research for the PIMS (Positioning In Macular hole Surgery) trial, a multicentre, interventional, comparative, randomised controlled clinical trial comparing face-down with face-forward positioning on the outcome for surgery for large macular holes. The PIMS trial is registered with ISRCTN, number 12410596 and the UKCRN portfolio, number 17966. The pilot study preceding PIMS was published in *Eye*, 2011 [1]. This pilot randomised controlled trial (RCT) explored the feasibility of a definitive trial to determine the value of face-down positioning following vitrectomy, internal limiting membrane (ILM) peeling, and C_3_F_8_ gas tamponade for full-thickness macular holes, without simultaneous phacoemulsification. The PIMS study protocol was published in *Trials*, 2015 [2]. We aim to maximise transparency of the planned analysis with the intention of eradicating misreporting or selective reporting of the trial data. We have also considered any contingences, with regards to specifying alternative analysis plans if statistical models fail to converge.

This analysis plan was written, reviewed and signed off prior to database lock, and prior to any member of the trial team having access to unmasked trial data.

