### Sample size

Clinical consensus is that face-down positioning would be recommended if there were a difference of 15% in success rates. This is the smallest clinically relevant treatment difference that we wish to detect. Previous research [6] indicates that successful closure of large macular holes without advice to position face-down occurs in 80% of cases. A study with 86 patients per group has 85% power and 95% confidence to detect a difference in outcome rate of 80% in the face-forward positioning arm versus 95% in the face-down positioning arm. With an anticipated 10% loss to follow-up, we are aiming to recruit 96 patients in each arm.

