### Variables measured and schedule of assessments

The variables measured preoperatively are age, sex, ethnicity, laterality, duration of symptoms, BCVA (Best-corrected Visual Acuity), lens status (either phakic or pseudophakic), macular hole diameter on OCT scans and the Quality of Life VFQ-25 questionnaireThe variables measured at 3 months postoperatively are BCVA, macular hole status (closed; open flat or open elevated), the Quality of Life VFQ-25 questionnaire, subject-reported experience of positioning and, if primary repair of a macular hole failed, was a second operation performed or planned?

For each comparison of outcomes according to positioning policy, the following summaries will be provided (see templates for tables in Additional file 1):The number of patients in each positioning policy group who are included in the analysisA summary measure of the outcome, by positioning policy group (mean and standard deviation (SD) for continuous outcomes, number and percentage in each category for categorical outcomes). The treatment effect (difference in means for continuous outcomes, odds ratio for binary outcomes) with its 95% confidence interval (95% CI) and *p* value

All comparisons will adjust for linear effect of macular hole size (μm) at baseline, phakic lens status at baseline, and a random effect of site (hospital). We will anonymise data reported by hospital site. Outcomes which are also assessed at baseline (BCVA and quality of life) will be analysed adjusting also for a linear effect of the baseline measurement.

Patients have a 2-week postoperative appointment, at which time clinicians may be able to identify that the macular hole closure was unsuccessful, meaning that a second operation to close the hole is required. The outcome of any participant who had a second surgery after randomisation but before the 3-month visit will be imputed as open, as it is most unlikely that the hole will close without further treatment by 3 months. These patients will not be completing secondary questionnaires.

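### The 0–10 positioning-experience score is to be dichotomised at a cut-off with no stated value or selection rule; analyse the full scale instead.

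*SAP article*

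**What the plan says.** The SAP article lists the positioning score among five secondary outcomes at 3 months (Outcome measures), from 0 for very difficult to 10 for very easy. Under Analyses of secondary outcomes the plan is: "we will remain masked to treatment arm and consider an applicable cut-off value to dichotomise this variable". The binary result then goes into xtlogit. The article states no value, no rule (such as a pooled median or a clinical anchor), no reason for dichotomising and no supporting analysis of the score itself.

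Three other statements bear on this:
- Variables measured and schedule of assessments sets the general rule for treatment effects: "difference in means for continuous outcomes, odds ratio for binary outcomes".
- Purpose and scope says "This analysis plan was written, reviewed and signed off prior to database lock", and describes the plan as written "with the intention of eradicating misreporting or selective reporting of the trial data".
- Participants, under Analysis methods, says that "the trial teams remain unmasked" at the time of writing.

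**The concern.** A signed-off plan should fix what will be estimated. Here the binary endpoint does not exist until someone picks a number, so its odds ratio has no meaning in advance. Patients scoring one point either side of the cut are treated as opposites, while those at the far ends of the same side are treated as alike.

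The treatment is also out of line with the rest of the plan. VFQ-25 is a bounded score expected to be skewed, yet its transformation and linear model are fixed in advance. For the question on whether patients would still have chosen the operation, the pooling of uncertain answers, a 10% trigger and a sensitivity analysis are all fixed. Only the positioning score is left open.

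The background describes face-down positioning as arduous. This score measures that burden directly, so it is what readers will weigh against any gain in closure. A loss of power or an arbitrary odds ratio matters for that comparison.

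**Working it through.** **Inputs.** The article gives no SD, distribution, effect size or power for this score. The only sample size is for the primary outcome: "A study with 86 patients per group has 85% power and 95% confidence", for "80% in the face-forward positioning arm versus 95% in the face-down positioning arm". A two-sided 5% test is assumed.

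**The plan's own figure.** With pooled proportion 0.875:

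n = [1.960·√(2·0.875·0.125) + 1.036·√(0.80·0.20 + 0.95·0.05)]² / 0.15² = 85.7, so 86 per arm. Power at 86 is 85.1%. Allowing for 10% loss, 86/0.90 = 95.6, so 96. The stated sample size reproduces, and 86 per arm is used below.

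**Information kept by a split, normal scores.** If a proportion q lies below the cut c, the efficiency relative to the full score is φ(c)²/[q(1−q)]. At the median this is 0.3989²/0.25 = 0.637.

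**Power.** Take an assumed difference δ = 0.46 SD, chosen because the full score then has about the trial's 85% power.
- Full score: Φ(0.46·√43 − 1.96) = Φ(1.056) = 85.5%.
- Median split: the effective δ is 0.46·√0.637 = 0.367, so Φ(0.367·√43 − 1.96) = Φ(0.447) = 67%.

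The last column enumerates the chi-square test exactly, with the two arms placed symmetrically about the split.

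| Split | Efficiency | Loss | Power, formula | Power, exact |
|---|---|---|---|---|
| none | 1 | 0 | 85% | – |
| 50/50 | 0.64 | 36% | 67% | 69% |
| 70/30 | 0.58 | 42% | 63% | 63% |
| 80/20 | 0.49 | 51% | 56% | 55% |
| 90/10 | 0.34 | 66% | 42% | 41% |

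Patients who have second surgery do not complete the secondary questionnaires, so fewer than 86 per arm may give a score. At an assumed 75 per arm, the formula gives 80% for the full score and 61% for a median split.

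**Other shapes.** These use 11 integer points. The first four take a latent normal score rounded and truncated to 0–10, with a shift of 0.4 latent SD. The loss at the best cut is:
- mean 5, SD 2.5: 34%
- mean 7, SD 2.5: 31%
- mean 8, SD 3 (ceiling): 24%
- mean 5, SD 6 (piled at both ends): 26%
- an assumed U-shape: about 10%

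A badly placed cut costs more. In the first case, splitting at 3 or above keeps 0.37 of the information, a loss of 63%.

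**Dependence of the result on the cut.** Take arms with latent means 6 and 4.85 and SD 2.5, a difference of 1.15/2.5 = 0.46 SD. As the threshold moves from 2 or above to 10, the odds ratio ranges from 2.1 to 2.7 and power from 26% to 69%. The same patients give different answers according to a number the plan does not state.

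**Type I error.** With no true difference and 86 per arm (20,000 simulated trials), a cut at the pooled median, chosen without sight of arm, rejected in 5.5%. Taking the best of six cuts with arms known rejected in 19%. Masking is therefore the safeguard that matters for the error rate.

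**The case against.** The strongest reply is that choosing masked to arm is a real safeguard. It is: pooled rules keep the error rate close to 5%. Further simulations with the pooled median and with the best two-cluster separation gave 5.1–5.8%, for both unimodal and bimodal scores. A reader might infer that the plan invites a cut tuned to the treatment effect, or that a large difference between arms would show up as two clusters and reveal the allocation. Neither reading stands. Two clusters split by arm would be a true, large effect, and a cut between them would measure it without creating a false positive. Power would not then be a worry either: a median split has 89% power at 0.6 SD and 98.8% at 0.8 SD.

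A reader might also take the cut to be chosen after the scores are seen. That is the natural reading, since staying masked matters mainly if pooled scores are being viewed. But the article does not say so, and a clinical anchor agreed while masked would also fit the wording.

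The statement that "the trial teams remain unmasked" looks like evidence that the safeguard is absent. It is very probably a slip. The article gives it as the reason for withholding the flowchart numbers, which makes sense only if the teams were masked. Purpose and scope also says that sign-off came before anyone on the team had access to unmasked data.

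It is fair, too, that a proportion is easy to explain to patients, and that the table templates in Additional file 1, not shown here, may already display the distribution. Neither supplies the missing cut or restores the lost information.

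**Conclusion.** The point holds in a limited form. The cut-off and the rule for choosing it are not specified, so the endpoint and its odds ratio are undefined in the signed-off plan. Dichotomising also gives up information that a simple model would keep.

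The size of the loss depends on assumptions that the documents cannot settle. About 36% is the smallest loss for roughly normal scores. It is not a general floor, because other plausible 11-point shapes lose about 10–34% at the best cut. The fall in power from 85% to 67–69% rests on an assumed 0.46 SD effect, 86 scores per arm and normality.

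The documents do not support a claim of inflated type I error, provided the masking is kept. The trial is not powered on this outcome, and the primary conclusion is unaffected.

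**What to change.** Make the full 0–10 score the main analysis, adjusted for macular hole size and lens status, with site as a random effect. Two options fit:
- xtreg with a difference in means, which follows the plan's own rule for continuous outcomes;
- an ordinal logistic model such as meologit, reporting a common odds ratio.

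Name one of them now, and tabulate the score distribution by arm.

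If a yes/no summary is kept, state the cut and its rationale before any scores are viewed, and label it supportive.

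Separately, correct the masking statement under Participants so that it agrees with Purpose and scope and with Analyses of secondary outcomes.

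The cost is a few lines of SAP wording and one model command. The downside is an assumption to check: linearity (an adequate mean-difference model for a bounded score) or proportional odds. Recruitment was still open when the article was submitted, so no data collection would need to change.

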## Outcome measures

The primary outcome of the study is the anatomical closure of the macular hole at 3 months post surgery.

Successful closure of the macular hole will be determined by OCT scans. The scans will be anonymised and sent to two independent retinal surgeons who will independently grade the macular hole as closed; ‘open and flat’ (without a cuff of subretinal fluid); or ‘open and elevated’ (with cuff of subretinal fluid). The readers will be masked to the identity and allocated treatment of the subject. In the event of any disparity in grading, a third independent retinal surgeon, also masked to identify and treatment allocation, will arbitrate.

The categories ‘open and flat’ (without a cuff of subretinal fluid), or ‘open and elevated’ (with a cuff of subretinal fluid) will be pooled into one category of ‘open’ for the purpose of analysis.

Secondary outcomes at 3 months post surgery are:Further surgery for macular holes, performed or planned (yes/no)Best-corrected visual acuity (BCVA) measured using a Snellen chart at a standard distance of 6 mPatient-reported experience of positioning on a scale from 0 (very difficult) to 10 (very easy)Patient-reported health and quality of life assessed using the National Eye Institute Visual Function Questionnaire (VFQ-25) from 0 (worst health and quality of life) to 100 (best health and quality of life)Patient-reported outcome ‘Given what you now know, would you still have elected to have the operation?’ with responses Yes, No or Don’t Know

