## Analysis methods

### General analysis principles

The primary analysis for each outcome will be by intention-to-treat, meaning that all patients on whom an outcome is available will be included in the analysis, and will be analysed according to the treatment group to which they were randomised.

Through vigilance and careful planning, the PIMS trial management team aim to achieve complete capture of all data from all patients, including patients who do not adhere to the protocol or patients who withdrawal from the trial. We acknowledge that despite our best efforts, some patients may have missing data. In accordance with the intention-to-treat principle and to avoid concerns over data-driven selection methods, we state the plan for dealing with missing data here.

Missing data is a potential source of bias, and the extent and pattern of missing data can influence the interpretation of the trial. The sample size for the PIMS trial allows for a 10% loss of follow-up, and in our results we will provide a full listing of all the reasons for patients’ withdrawal of the study. This list will be helpful in justifying the assumptions that we make in regards to missing data; however, we cannot be certain that there is a relationship between observed covariates and missing outcome data, and cannot exclude the possibility of some data missing not at random.

We will analyse the data without undertaking any sensitivity analysis if the primary outcome is missing in fewer than 5% of cases (nine patients or less). If more than nine patients’ primary outcome is missing, we will undertake sensitivity analysis to test if the missing at random assumptions are appropriate. We will use a pattern-mixture approach to model the consequences of a systematic difference between missing and nonmissing values, to see if the conclusions drawn from the PIMS study are affected when the missing-at-random assumption is violated.

All analyses will be performed using Stata (Stata Corporation, College Station, TX, USA).

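### The VFQ-25 transformation log(x/(100 − x)) has no value at scores of 0 and 100, so patients with those observed scores would leave an analysis that is meant to include them

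*SAP article*

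**What the plan says.** All of the text is in the SAP article.

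- *Outcome measures* describes the VFQ-25 as scored "from 0 (worst health and quality of life) to 100 (best health and quality of life"), so both ends belong to the scale.
- *Analyses of secondary outcomes* cites skewness in another trial and says "we will assume that our results will be similarly skewed, and perform a logistic transformation", with the formula log(x/(100 − x)). The formula is applied to all "of the VFQ-25 scores, and with this transformed outcome use linear regression" (xtreg).
- The same section extends it to the covariate: "we will use the same normalising transformation for the baseline measurement as for the follow-up measurement".
- *General analysis principles* sets the analysis population: "all patients on whom an outcome is available will be included in the analysis". It also names the software: "All analyses will be performed using Stata".

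No offset, truncation or substitute value is given for a VFQ-25 score of 0 or 100. By contrast, the same section does give numerical replacements for visual acuity too poor for the Snellen chart (2.10, 2.40, 2.70 and 3.00).

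**The concern.** The plan fixes an exact formula that fails at two attainable values of its own scale. A patient who reports the best possible visual function at 3 months has an observed outcome, yet cannot enter the model. The same holds for a patient at either extreme at baseline, because the covariate is transformed in the same way.

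Two things are at stake. First, dropping a patient because the follow-up score is 100 (or 0) is selection on the outcome. If the arms differ in how often this happens, the comparison is biased. The missing-data sensitivity analysis would not pick this up, since it is triggered only by missing primary outcomes. Second, an analyst who notices the problem must choose a substitute value after scores have been seen. The result can depend on that choice, which is what a published plan is meant to prevent.

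**Working it through.** **Inputs.** Score range 0 to 100 (*Outcome measures*); transformation log(x/(100 − x)) at both visits and xtreg (*Analyses of secondary outcomes*); 86 per group expected at follow-up and 96 recruited per arm (*Sample size*). The plan states no figure for the share of extreme scores and no power for the VFQ-25.

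**The plan's own figure.** With 80% versus 95%, two-sided 5% and 85% power, the pooled-variance formula without continuity correction gives n = [1.96 × √(2 × 0.875 × 0.125) + 1.036 × √(0.8 × 0.2 + 0.95 × 0.05)]² / 0.15² = 85.7, so 86 per group. Then 86/0.9 = 95.6, so 96. Both figures reproduce. The sample size is used below only to give 2 × 86 = 172 patients followed up.

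**Step 1: the end points.**

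- x = 100: 100/(100 − 100) divides by zero.
- x = 0: log(0/100) = log(0), which is not finite.

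Stata returns missing for both, and xtreg omits any record with a missing outcome or covariate.

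**Step 2: how many patients.** Let q0 and q1 be the shares with a score of exactly 0 or 100 at baseline and follow-up. These are assumptions, and the two visits are treated as independent. Expected loss = 172 × [1 − (1 − q0)(1 − q1)].

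| q0 | q1 | Expected loss |
|---|---|---|
| 0 | 0 | 0 |
| 0 | 1% | 1.7 |
| 1% | 2% | 5.1 |
| 1% | 5% | 10.2 |
| 2% | 10% | 20.3 |

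The base of 172 is itself generous: patients with a second operation before 3 months do not complete the questionnaires, and their number is not stated.

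**Step 3: does a later choice of substitute matter?** Replacing a score of 100 by 99.9, 99.5 or 99 gives log(99.9/0.1) = 6.9, log(99.5/0.5) = 5.3 or log(99/1) = 4.6. A score of 95 gives log(95/5) = 2.9. The transformed value for a perfect score therefore moves by 2.3 logits according to a choice that the plan does not make.

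**Step 4: a formula that is defined everywhere.** With log((x + 0.5)/(100.5 − x)):

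- x = 100: log(100.5/0.5) = 5.30
- x = 0: log(0.5/100.5) = −5.30
- x = 95: log(95.5/5.5) = 2.85, against 2.94 under the present formula
- x = 50: 0 under both

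Every observed score is kept. At 95 the change is 0.09 logits.

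**The case against.** The case for leaving the plan alone has several sound parts.

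- **The number affected may be nil.** Nothing in the document shows that anyone will score exactly 0 or 100. All participants enter with a full-thickness hole and a history of visual loss, which makes a perfect baseline score less likely, though not impossible. This stands and limits the size of the point.
- **Losses would be visible.** *Variables measured and schedule of assessments* requires the number of patients included in each comparison, by group. A reader might infer that patients vanish silently; the plan's own reporting rule does not support that. Visibility does not undo the exclusion, however.
- **Fixing the transformation in advance is defensible.** A reader might object that it is borrowed from a different disease. Specifying it before unmasked data are seen serves the plan's aim of preventing selective reporting, and the suitability of the cited trial cannot be judged from this document.
- **Stretching near 100.** A 5-point step from 50 to 55 is log(55/45) − log(50/50) = 0.20 logits; from 94 to 99 it is log(99/1) − log(94/6) = 1.84. A reader might infer that patients just below 100 dominate the treatment effect. These figures describe the scale at two chosen places, not regression weight. Without the score distribution, dominance is not shown, and spreading out a crowded end is what a logit is for.
- **Units.** The plan promises, for continuous outcomes, "mean and standard deviation (SD) for continuous outcomes" and "The treatment effect (difference in means for continuous outcomes, odds ratio for binary outcomes"). A reader might infer an effect in VFQ-25 points, but the text does not say so; a difference in mean logits is compatible with it. The table templates that might settle this are in an additional file that is not shown.

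None of this answers the core point. The formula is undefined at two values that the plan allows, and the inclusion rule cannot be met for patients who have them. Nor is this detail that an article would leave to a fuller document: the exact formula is printed, and off-chart acuity is handled in the same paragraph.

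**Conclusion.** The concern holds in a limited form. As written, the VFQ-25 rule cannot be applied at 0 or 100, removes such patients at either visit, and contradicts the stated analysis population; at follow-up it does so because of the outcome. This follows from the formula and the stated range, together with Stata's ordinary handling of undefined values, and needs no assumption about the data.

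The size does need one. The share of extreme scores is unknown; the assumed ranges above give 0 to about 20 of 172 patients, and zero is a real possibility. It would overstate the matter to call this a must-fix: the VFQ-25 is one of five secondary outcomes, and the primary analysis and sample size are untouched.

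**What to change.** Before unmasking, replace the VFQ-25 formula with one defined over the whole range, for example log((x + 0.5)/(100.5 − x)), and apply it at baseline and follow-up alike.

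Add one sensitivity analysis: the untransformed 0–100 score, adjusted for its baseline and the plan's other covariates, with a robust or bootstrap 95% CI. It shows whether the conclusion depends on the offset and gives a difference in VFQ-25 points.

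The cost is about a sentence of wording, one changed line of code and one extra analysis. The offset is arbitrary, and it does not remove the stretching near the top: 94 to 99 is still log(99.5/1.5) − log(94.5/6.5) = 1.52 logits, against log(55.5/45.5) = 0.20 for 50 to 55. That is a further reason for the untransformed analysis alongside. Making the untransformed score the main analysis would be a legitimate alternative, but it is a trade-off, since inference then rests on large-sample or bootstrap methods for skewed scores. The defect does not require it.
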